## Abstract

**Background:**

Normofractionated radiation regimes for definitive prostate cancer treatment usually extend over 7–8 weeks. Recently, moderate hypofractionation with doses per fraction between 2.2 and 4 Gy has been shown to be safe and feasible with oncologic non-inferiority compared to normofractionation. Radiobiologic considerations lead to the assumption that prostate cancer might benefit in particular from hypofractionation in terms of tumor control and toxicity. First data related to ultrahypofractionation demonstrate that the overall treatment time can be reduced to 5–7 fractions with single doses > 6 Gy safely, even with simultaneous focal boosting of macroscopic tumor(s). With MR-guided linear accelerators (MR-linacs) entering clinical routine, invasive fiducial implantations become unnecessary. The aim of the multicentric SMILE study is to evaluate the use of MRI-guided stereotactic radiotherapy for localized prostate cancer in 5 fractions regarding safety and feasibility.

**Methods:**

The study is designed as a prospective, one-armed, two-stage, multi-center phase-II-trial with 68 patients planned. Low- and intermediate-risk localized prostate cancer patients will be eligible for the study as well as early high-risk patients (cT3a and/or Gleason Score ≤ 8 and/or PSA ≤ 20 ng/ml) according to d’Amico. All patients will receive definitive MRI-guided stereotactic radiation therapy with a total dose of 37.5 Gy in 5 fractions (single dose 7.5 Gy) on alternating days. A focal simultaneous integrated boost to MRI-defined tumor(s) up to 40 Gy can optionally be applied. The primary composite endpoint includes the assessment of urogenital or gastrointestinal toxicity ≥ grade 2 or treatment-related discontinuation of therapy. The use of MRI-guided radiotherapy enables online plan adaptation and intrafractional gating to ensure optimal target volume coverage and protection of organs at risk.

**Discussion:**

With moderate hypofractionation being the standard in definitive radiation therapy for localized prostate cancer at many institutions, ultrahypofractionation could be the next step towards reducing treatment time without compromising oncologic outcomes and toxicities. MRI-guided radiotherapy could qualify as an advantageous tool as no invasive procedures have to precede in therapeutic workflows. Furthermore, MRI guidance combined with gating and plan adaptation might be essential in order to increase treatment effectivity and reduce toxicity at the same time.

## Background

In 2021, the estimated number of new prostate cancer cases was 248,530 in the US accounting for 26% of all new cancer cases in males [1]. Worldwide, the number of new prostate cancer cases was 1,414,259 in 2020 [2]. Due to its high prevalence and demographic changes towards growing proportions of elderly people in many western countries, there is a need for effective treatment alternatives, both in terms of outcome and economic burden of the health care system. Also, the COVID-19 pandemic has shown that reduced treatment times can be beneficial with regard to limited treatment capacities. In primary treatment of prostate cancer, definitive radiation therapy plays a major role. Apart from surgical options, various treatment options are available for intermediate-risk (IR) and low-risk (LR) disease, including active surveillance and brachytherapy for the latter. Normofractionated image-guided intensity-modulated radiotherapy (IG-IMRT) has been the standard radiation scheme at many institutions, usually extending over 7–8 weeks [3]. Moderate hypofractionation using single doses between 2.4 and 3.4 Gy/fraction has been shown to achieve very good clinical outcomes compared to normofractionated radiotherapy in patients with prostate cancer [4–7]. The CHHiP trial, one of the largest of these studies, having included more than 3000 patients with localized prostate cancer, demonstrated noninferiority of moderate hypofractionation with 60 Gy in 20 fractions compared to conventional fractionation [4]. Therefore, moderate hypofractionation has become a recommended alternative in the German S3-guideline. Radiobiologic considerations based on the linear-quadratic model lead to the assumption that prostate cancer might in particular benefit from hypofractionation in terms of tumor control and toxicity. The α/β value as measure of fractionation sensitivity is considered to be relatively low for prostate cancer cells in relation to its surrounding normal tissues, predicting higher sensitivity to fractional doses without compromising toxicity. Several preclinical and clinical studies have suggested α/β values of about 1.5 Gy for prostate cancer cells, which would theoretically lead to a better therapeutic ratio [8–13]. Considering the overall treatment time as another factor in calculation of the α/β value results in higher values of about 2–2.7 Gy [14]. In recent years, many patients have been treated with ultrahypofractionated radiation regimes, reducing treatment to 3–10 fractions with a major part of published data focusing on regimes with only 5 fractions. Those studies showed excellent biochemical control rates of 93–100% after 1–5 years in patients with LR or IR disease [15–22]. Widmark et al. were the first to publish 5-year-results of a randomized phase III study, demonstrating non-inferiority of ultrahypofractionated radiation with 42.7 Gy in seven fractions 3 days per week compared to 78 Gy in 39 fractions with regard to failure-free survival and late toxicity [23]. When using normofractionation, the addition of a focal boost up to 95 Gy to MR-defined macroscopic tumor(s) improved biochemical disease-free survival (bDFS) in the recent FLAME phase III trial without compromising toxicity in patients with IR and HR disease [24]. Furthermore, first toxicity data from the phase II hypo-FLAME trial showed that the addition of simultaneous focal boosting to the macroscopic tumor(s) to ultrahypofractionated SBRT of the prostate gland is safe with no grade ≥ 3 acute GU or GI toxicity and acceptable rates of grade 2 toxicities[25].

As MR-guided linear accelerators (MR-linacs) have entered clinical routine, new aspects in terms of image guidance and plan adaptation promise to further improve stereotactic body radiation therapy (SBRT) outcomes. Whereas cone-beam CTs or other X-ray based systems involve radiation exposure, image guidance using integrated MR imaging does not. One of the major advantages using magnetic resonance-guided radiotherapy (MRgRT) is the ability to visualize target volumes such as the prostate or organs at risk (OAR) before, after but also during radiation therapy [26]. This seems to increase accuracy of targeting and enables sparing of radiation dose to OAR in particular when using hypofractionation. First published data of clinical use are promising. In locally advanced pancreatic cancer, SBRT with 24 Gy in 3 fractions could safely be applied without higher grade toxicity [27, 28]. Data by Rudra et al. found that high dose SBRT (biologically effective dose [BED_10Gy_] > 70 Gy) using adaptive MRgRT for treatment of inoperable pancreatic cancer patient resulted in improved overall survival rates compared to standard doses [29]. We see great potential in the use of MRgRT for prostate SBRT, as OAR such as the rectum can be monitored closely in order to reduce therapy-related toxicity. On the other hand, the target volume itself can be displayed with excellent quality, which could result in higher treatment effectivity [30].

The aim of this prospective, multicentric phase II trial is to evaluate the incidence and grade of genitourinary (GU) and gastrointestinal (GI) toxicity and the incidence of treatment-related discontinuations of therapy in patients with local LR and IR as well as early high-risk prostate cancer patients. It is the first prospective phase II trial combining MR-guided SBRT with optional simultaneous focal boosting of macroscopic tumor(s). The greater aim is to generate data for following trials, which could in the long term establish MRgRT in combination with ultrahypofractionation as a potential new time-saving and economically favorable option for the named patient groups.

## Methods

### Study design

The study is designed as a prospective, one-armed, two-stage, multi-center phase-II-trial, evaluating the safety and feasibility of extreme hypofractionated radiotherapy with MRgRT in localized prostate cancer. After obtaining written informed consent, patient fulfilling the inclusion criteria will undergo treatment planning with non-contrast enhanced simulation MR imaging at the linac and standard computer tomography. Multi-parametric magnetic resonance imaging (mpMRI) of the prostate is included in the study protocol as an optional procedure. Fiducials should not be implanted into the prostate gland. Radiation therapy is applied as MRI-guided intensity-modulated radiation therapy (IMRT) with gated dose delivery. Online plan adaptation should be performed at every treatment session. Systemic treatments, e.g. androgen deprivation therapies are not part of this study and should be handled according to current therapy guidelines.

### Study objectives

The hypothesis of our study is that stereotactic MRI-guided radiotherapy is safe for patients with low-, intermediate- and early high-risk prostate cancer. The primary endpoint of our study is a composite endpoint with the occurrence of either any genitourinary (GU) or gastrointestinal (GI) toxicity ≥ grade 2 within one year after start of radiotherapy or treatment-related discontinuation of therapy being an event. Secondary endpoints include treatment-related mortality within one year and within 5 years after start of radiation therapy, GU and GI toxicity graded according to NCI CTCAE version 5.0 after one and five years from treatment start, biochemical progression free survival (bPFS) since treatment start defined as PSA recurrence according to the phoenix criteria (post-therapeutic nadir of PSA + 2 ng/ml) and androgen deprivation therapy (ADT) free survival (3 months of neoadjuvant ADT is allowed). Furthermore, secondary endpoints include overall survival (OS) and quality of life (QOL), assessed with EORTC QLQ-C30 und -PR25 questionnaires during and after treatment. Planning and treatment parameters as well as imaging and quality assurance results are assessed for further evaluation.

### Patient population/patient selection

Inclusion criteria according to the protocol are:Histologically confirmed prostate cancer with Gleason-score grading and PSA parametersLow-/intermediate- and early high-grade (cT3a/and or Gleason Score 8 and/or PSA ≤ 20 ng/ml) risk group according to d’Amico criteriaInternational Prostate Symptom Score (IPSS) of ≤ 12Prostate gland volume < 80 cm^3^Karnofsky Index ≥ 70%Age ≥ 18 yearsWritten informed consent

Exclusion criteria are the following:Patient’s refusal or incapability of informed consentPrior pelvic radiation therapyPrior local therapy of the prostate glandLymphogenic metastasesStage IV (distant metastases)Contraindication to undergo MRIParticipation in another clinical trial which might influence the results of the SMILE study

### Sample size calculation

In order to estimate the sample size of our prospective phase II trial, we followed data published by Bruynzeel et al. [30]. In their MRgRT prostate SBRT trial with 5 × 7.25 Gy, the maximum cumulative grade ≥ 2 early GU and GI toxicity was 23.8%. We hypothesize that the rate of treatment-related therapy discontinuations can be neglected. It is our goal to show that the rate of events is below a clinically acceptable limit of 40%. A sample size of 68 patients with a planned interim analysis after 30 patients was calculated in order to be able to reject the null hypothesis at the one-sided significance level of α = 0.025 with a statistical power of 80%. We chose Simon’s two stage design to reduce the expected number of patients under the null hypothesis compared to a single stage design, as a premature study termination with acceptance of the null hypothesis is possible [31, 32]. If the null hypothesis is true, the expected sample size is 42. As a discontinuation of therapy is included in the primary composite endpoint, missing values are not to be expected. The sample size calculations were performed using R (Version 3.6.1) with the R package OneArmPhaseTwoStudy [33].

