## Discussion

The Scandinavian trial by Widmark et al. is the only study so far that has reported non-inferior outcome and toxicity 5 years after normofractionated vs. ultrahypofractionated radiotherapy for intermediate-risk and a small proportion of high-risk prostate cancer patients [23]. Another non-inferiority trial, PACE-B, compared conventionally fractionated, moderately hypofractionated radiotherapy (78 Gy in 39 fractions over 7–8 weeks or 62 Gy in 20 fractions over 4 weeks, respectively) and SBRT with 36.25 Gy in five fractions over 1–2 weeks. For PACE-B early toxicity results are available, showing no significant difference between the treatment arms with a slight trend in favor of the SBRT regime (23% vs. 27%) [38]. In the HYPO-RT-PC trial, acute grade 2 or worse genitourinary toxicity was slightly but not significantly higher in the SBRT (42.7 Gy in 7 fractions) arm (28% vs. 23%, p = 0.057) compared to normofractionation (78 Gy in 39 fractions) at the end of radiation therapy. The difference was significant after one year (6% vs. 2%, p = 0.0037), but disappeared after five years. GI toxicity was not significantly different at any timepoint. MR imaging for target volume delineation or usage of IMRT were not mandatory in that trial, resulting in a large proportion of patients treated with 3D-conformal RT [23]. In PACE-B, Cyberknife and conventional LINACs were used with mandatory IGRT and intra-fractional motion control. The only prospective data for MRgRT with an ultrahypofractionated treatment regime were published by Bruynzeel et al., reporting relatively low early GI and GU toxicity (23.8% and 5.0% respectively for the maximum cumulative grade ≥ 2 toxicity at any study time point), with the majority of enrolled patients having high-risk disease (59.4%) [30]. Bruynzeel et al. reported a peak of GU toxicity at the end of treatment and discussed that their chosen 6 weeks follow up time point may have obscured very early increases in toxicity after the end of RT. Therefore, we planned a first assessment of toxicity 4 weeks after the end of RT (Table 1) [39]. The FLAME phase III trial has demonstrated that focal boosting to intraprostatic lesion in normofractionated RT is safe and improves bDFS (92% vs. 85% after 5 years) without compromising toxicity and quality of life compared to standard treatment without boost [24]. The same group’s hypo-FLAME trial is now following up patients treated with SBRT (35 Gy in 5 weekly fractions) with an integrated boost up to 50 Gy to mpMRI-defined tumor lesions. First published toxicity data are promising, showing no acute ≥ grade 3 toxicities and acceptable 34.0% and 5.0% grade 2 GU and GI toxicities [25]. MRgRT generally offers various advantages such as using small CTV to PTV margins, online CTV monitoring, daily plan reoptimization and the avoidance of gold marker implantation. The latter is in particular beneficial for patients, obviation additional invasive procedures with encompassing risks such as infection. On the other hand, it is more time-consuming and cost intensive compared to other SBRT techniques. Questions regarding cost-effectivity will have to be answered in future analyses. The aim of our study is to assess the safety and feasibility of ultrahypofractionated MRgRT in a prospective setting. The innovative approach of our trial clearly is the combination of MRgRT with ultrahypofractionated SBRT, allowing focal integrated boosting of mpMRI-defined tumor lesions.

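### The 80% power rests on a 23.8% event rate that the Discussion reports as the rate of one toxicity domain; for the either-domain endpoint, the article's own figures put power between about 47% and 80%

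*Protocol article*

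**What the plan says.** The Sample size calculation draws its planning rate from one published MR-guided prostate SBRT trial, stating that the highest cumulative rate of grade ≥ 2 "early GU and GI toxicity was 23.8" per cent. Treatment-related discontinuation is taken as negligible. The aim is to show that "the rate of events is below a clinically acceptable limit of 40" per cent, at a "one-sided significance level of α = 0.025 with a statistical power of 80" per cent. The design is given as "A sample size of 68 patients with a planned interim analysis after 30 patients", with an expected size of 42 under the null hypothesis. The Statistical analysis section stops the trial at 11 or more events among the first 30 evaluable patients, and otherwise recruits 38 more.

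The Discussion describes the same reference trial as having "relatively low early GI and GU toxicity (23.8% and 5.0% respectively", again for the maximum cumulative grade ≥ 2 toxicity.

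Under Study objectives, the primary endpoint is grade ≥ 2 toxicity in either the GU or the GI domain "within one year after start of radiotherapy or treatment-related discontinuation of therapy being an event".

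**The concern.** The two sections disagree on what 23.8% measures. The Sample size calculation reads it as one figure covering both domains. The Discussion attaches it to one domain and gives the other its own 5.0%. If the Discussion is right, the planning rate describes a narrower event than the endpoint, because a patient with an event only in the 5.0% domain would count as an event in this trial but is not in the 23.8%.

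The design just reaches 80% at 23.8%, so even a small upward correction takes power below the stated value. At stake is the chance of a false-negative result: a treatment performing as the reference did could fail to show a rate below 40% more often than the stated 20%, and that failure could be misread as evidence against the treatment.

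**Working it through.** **Inputs.** From the Sample size calculation: p0 = 0.40, p1 = 0.238, one-sided α = 0.025, N = 68, first stage 30. From the Statistical analysis section: continue if there are 10 or fewer events in 30; second stage 38. From the Discussion: domain rates of 23.8% and 5.0%. Not given in the article: the final cut-off c and the overlap between domains.

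**Formula.** The null hypothesis is rejected if stage 1 has at most 10 events and the total is at most c:

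P(reject | p) = Σ over x = 0 to 10 of P[Bin(30, p) = x] × P[Bin(38, p) ≤ c − x].

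**Final cut-off.** I took the largest c that keeps α ≤ 0.025 at p = 0.40:

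- c = 18: α = 0.0133
- c = 19: α = 0.0241
- c = 20: α = 0.0407, too large

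Hence c = 19.

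**Reproducing the plan's figures.** At p = 0.238 and c = 19, power is 0.8016, which matches the stated 80%. Under the null hypothesis the probability of stopping at the interim is 0.7085, so the expected size is 30 + 38 × (1 − 0.7085) = 41.1, consistent with the stated 42 if rounded up. The design was therefore evaluated at, or very close to, 23.8%, with nothing added for a second domain.

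**Either-domain rate on the Discussion's figures.** Rate = 23.8% + 5.0% × (1 − s), where s is the share of patients with an event in the 5.0% domain who are already counted in the 23.8%.

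- s = 1 gives 23.8%.
- s = 0.5 gives 23.8 + 2.5 = 26.3%.
- Independence (s = 0.238) gives 1 − 0.762 × 0.950 = 27.6%.
- s = 0 gives 23.8 + 5.0 = 28.8%.

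**Power at these rates, same design, c = 19.**

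| Overlap assumed | Either-domain early rate | Power |
|---|---|---|
| Complete | 23.8% | 80.2% |
| Four fifths | 24.8% | 74.5% |
| Half | 26.3% | 64.8% |
| Independence | 27.6% | 55.6% |
| None | 28.8% | 47.1% |

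Even if four fifths of the smaller domain's patients are already counted, power is below 75%.

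**What the table leaves out.** These are early rates. For a cumulative endpoint, events between the early period and one year, and any treatment-related discontinuations, can only add to the composite rate. The article gives no figure for either.

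**The case against.** The strongest reply is that there is no arithmetic error. Power is always conditional on an alternative, the section names 23.8%, and at 23.8% the 80% is correct. That stands: the fault lies in what the planning figure is said to represent, not in the calculation from it.

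A second reply is that the Discussion may be the section in error. Its sentence assigns 23.8% to GI and 5.0% to GU, yet the text that follows on the same trial discusses a GU peak, so the labels may be reversed. Without the cited report, the patient-level either-domain rate cannot be known. This also stands, and it is why the point is a contradiction to be reconciled and a range to be stated. A swap of labels leaves the power figures unchanged.

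Third, the study is called exploratory, type I error does not depend on p1, and a higher true rate raises the risk of a false negative and not of a false claim of safety. That limits the consequences. It does not excuse the stated power, since the section sets a null hypothesis, an α and a power.

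Three stronger readings are tempting but unsupported.

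- **That power is really about 47–56%.** This requires independence or less overlap. Positive association between the domains would put power above 56%, and complete overlap remains possible.
- **That the reference trial's higher-risk patients, or this trial's higher dose and optional boost, settle the direction of the error.** This trial also restricts baseline symptom score and gland volume and gives organ-at-risk constraints first priority. These may pull the other way, and the net effect cannot be quantified from the article.
- **That the 34.0% grade 2 GU rate quoted in the Discussion for another boosted SBRT trial is the relevant alternative.** That trial used weekly fractions and a boost up to 50 Gy, so its rate does not carry over.

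**Conclusion.** The concern holds as a contradiction about the number behind the stated power. On the Discussion's figures the 80% holds only if essentially every patient with an event in the 5.0% domain is already among the 23.8%; otherwise power lies between about 47% and 80%. Where it falls in that range depends on an overlap the article does not report, so no single lower value can be called the true power.

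The range rests on three assumptions: the Discussion's two rates are correct, the final cut-off is at most 19 events in 68 (derived, since the article states none), and the early rate stands in for the one-year composite with discontinuations at zero. The third is favourable to the plan, by an unknown amount.

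**What to change.** 1. Reconcile the Sample size calculation with the Discussion on what 23.8% measures and to which domain it belongs.
2. State the composite event rate assumed for the primary endpoint. If the sponsor holds the reference trial's patient-level either-domain rate, cite it and give power at that rate.
3. If not, restate power as about 47–80% over a composite rate of 23.8–28.8%, name the overlap between domains as an assumption, and show intermediate values such as 65% at 26.3% and 56% at 27.6%.
4. Add a sentence that events after the early period up to one year, and any treatment-related discontinuations, can only raise the composite rate, by an amount not quantified.

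This is a change of wording only. Sample size, interim rule and boundaries can stay, and type I error is unaffected. The cost is a less favourable stated power.

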### Statistical analysis

The statistical analysis includes all enrolled patients (Intention-to-treat- (ITT) population). Additionally, a per-protocol- (PP) analysis will be performed. Since this is an exploratory study all results will be interpreted descriptively. An interim analysis will be conducted when 30 patients are evaluable for the primary endpoint. If an event is observed in at least 11 of these patients (corresponding to 37%), the study will be terminated with acceptance of the null hypothesis. In case of 10 or fewer events the study will be continued with recruitment of 38 additional patients.

A 95% confidence interval, correcting for the two-stage design, will be calculated for the event rate of the primary endpoint. Kaplan–Meier curves will be computed for all survival endpoints. Regression models will be used to analyze factors influencing the different endpoints. Missing values will not be imputed.

